**Table 3 Tab3:** **Composite endpoint diabetes related complications**

Diabetes related complications	Definition
Hypoglycaemia	For which assistance was required
Diabetic Ketoacidosis	For which admission was required
Seeking medical help	Unplanned appointment with physician or DM nurse
Change in medication	Change in dose or medication stopped within 30 days of surgery
New medication	Additional diabetes medication started within 30 days of surgery

### Randomisation

If eligible, patients will be randomised into one of the three study arms. The randomisation will be 1:1:1 for each study arm, with stratification for insulin use. We will use block randomisation with random block sizes, ranging from 3 to 12. The randomisation will be performed with a computer based randomisation application (TENALEA Clinical Trial Data Management System). Patients and investigators are not blinded for the treatment allocation. All patients randomised will be included in the intention to treat analysis.

### Study procedures/interventions

In all patients, capillary glucose will be measured every 60 minutes, starting 30 min prior to surgery. The target range for plasma glucose for all study arms is 6–8 mmol l^−1^. An intravenous bolus of insulin will be administered according to treatment algorithm (Table 4). Capillary glucose will be measured using the Accu-Chek Inform (Roche diagnostics, Indianapolis, IL, USA).

**Table 4 Tab4:** **Treatment algorithm**

Glucose measurement*	Insulin 1st bolus	If glucose increases after 1st bolus	If glucose increases after 2nd bolus
4-8 mmol/l	-	-	-
8-9 mmol/l	2 IU	4 IU	6 IU
9-10 mmol/l	3 IU	5 IU	7 IU
10-11 mmol/l	4 IU	8 IU	12 IU
11-12 mmol/l	5 IU	9 IU	13 IU
12-13 mmol/l	6 IU	12 IU	18 IU
13-14 mmol/l	7 IU	13 IU	19 IU
14-15 mmol/l	8 IU	15 IU	20 IU
15-16 mmol/l	9 IU	16 IU	21 IU
> 16 mmol/l**	10 IU	17 IU	22 IU

*If glucose is <4 mmol l^−1^, give 4 g glucose iv (20 ml glucose 20%) measure again after 10 minutes and consult research physician. If glucose is <2.3 mmol l^−1^ give 50 g glucose iv. (100 ml glucose 50%) measure again after 10 minutes and consult research physician. **Consult research physician. (multiply by 18 for mg dl^−1^).

Subjects in the glucose-insulin-potassium arm (GIK) will receive:

The day before surgery, the evening dose of long acting insulin will be reduced with 50%.On the day of surgery, the regular insulin dose, if applicable, and the oral glucose lowering tablets will be withheld.GIK infusion: 10 mmol potassium-chloride and a calculated insulin dose are added to a 500 ml glucose 5% solution. The infusion is started 30 minutes before surgery at 83 ml/hr. The insulin dose in the GIK infusion will be calculated according to the formula:○ I = (PG-7)/(200/W) + 8 I = Insulin amount, PG = glucose 30 minutes preoperative, W = body weight in kg.Measure glucose every 60 minutes after start of surgery, start 30 min prior to surgery○ If glucose is 4–6 mmol l^−1^ stop infusion and measure again in 30 minutes○ If glucose is <4 mmol l^−1^, give 4 g glucose iv. (20 ml glucose 20%),○ measure again after 10 minutes and consult research physician.○ If glucose is <2.3 mmol l^−1^, give 50 g glucose iv. (100 ml glucose 50%),measure again after 10 minutes and consult research physician.○ If glucose is >8 mmol l^−1^, treat according to algorithm.

Subjects in the insulin Bolus Regimen arm (BR) will receive:

The day before surgery, the evening dose of long acting insulin will be reduced by 50%.On the day of surgery:○ *If patients are using mealtime and longacting insulin/NPH*: mealtime morning dose will be withheld.○ *If patients are using only long acting insulin/NPH*: the dose of long-acting or NPH insulin will be reduced by 50%○ *If patients are using glucose lowering tablets*: glucose lowering tablets will be withheld on the morning of surgery.Measure glucose every 60 min, start 30 min prior to surgeryAdjust glucose according to treatment algorithm

Subjects in the liraglutide arm (LG) will receive:

On the day before surgery 0.6 mg liraglutide will be administered subcutaneously (s.c.) at 17.00 hr (5 pm). The dose of long acting and mealtime insulin will be reduced by 50% from the start of liraglutide treatment.On the day of surgery own insulin and oral glucose lowering tablets will be withheld.In case of nausea graded higher than minimal, the second gift of liraglutide will be omitted. Otherwise, treatment will be continued with 1.2 mg liraglutide s.c. on the morning of surgery.Measure glucose every 60 min, start 30 min prior to surgeryAdjust glucose according to treatment algorithm

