### Postoperatively

The assigned treatment will be continued up to 4 hours postoperatively. The patient will stay at the recovery room and will remain fasted. The treatment protocol will end 4 hours postoperatively. Hereafter, glucose will be monitored and treated according to the hospital protocol.

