### Outcome measures

Our primary outcome measure is the difference in median serum glucose between the GIK, BR and LG arm 1 hour after surgery.

The secondary outcome measures are the difference in median serum glucose between the three study arms at 4 hours and 1 day postoperatively, the difference in the amount of insulin administered and difference in the occurrence of major, minor and diabetes related complications. the hourly measurements will be used to determine the perioperative area under the curve of the area outside the target range. In addition, the occurrence of mild or severe hypoglycaemia (glucose <4.0 mmol l^−1^ and <2.3 mmol l^−1^, respectively), hypokalaemia (<3.5 mmol l^−1^) or hyperkalaemia (>5.0 mmol l^−1^) is assessed. The difference in glucose variability, described as mean absolute glucose change (MAG), between study arms will be calculated [24]. The MAG is calculated by adding the absolute differences of the glucose values, divided by the time over which the measurements were taken.

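### GIK arm: the only stop instruction covers 4–6 mmol/l, so readings the protocol itself calls hypoglycaemia carry no stated stop or do-not-start of the insulin infusion (minor)

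*Protocol article*

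**What the plan says.** The GIK rules are printed under Study procedures/interventions, after Table 4. On the infusion: "The infusion is started 30 minutes before surgery at 83 ml/hr". The bag is 500 ml of glucose 5% with 10 mmol potassium chloride and an insulin dose calculated from preoperative glucose and body weight.

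Four glucose rules follow:

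- **4–6 mmol/l:** "stop infusion and measure again in 30 minutes".
- **Below 4 mmol/l:** 4 g intravenous glucose, then "measure again after 10 minutes and consult research physician".
- **Below 2.3 mmol/l:** 50 g intravenous glucose, with the same recheck and consultation.
- **Above 8 mmol/l:** insulin boluses from Table 4.

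The Table 4 footnote gives the same two low-glucose steps for all three arms, again without mentioning an infusion; for the lower band it reads "100 ml glucose 50%) measure again after 10 minutes and consult research physician".

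On monitoring: "capillary glucose will be measured every 60 minutes, starting 30 min prior to surgery". Outcome measures lists "the occurrence of mild or severe hypoglycaemia" as an outcome, with cut-offs of 4.0 and 2.3 mmol/l.

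**The concern.** A rule for stopping insulin should apply at every reading at or below its threshold. This one has a floor as well as a ceiling. It acts at 5 mmol/l and is silent at 3.5 or 2.0, where the case for stopping is stronger.

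A likely cause is visible in the text. The two low-glucose rules repeat the all-arm footnote. That footnote needs no stop in the bolus and liraglutide arms, which have no insulin infusion, but the GIK arm does have one.

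What is at stake is a clear bedside instruction for a patient who is already hypoglycaemic. The Background itself reports poor adherence to diabetes protocols, which is a reason to leave nothing to inference.

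**Working it through.** The protocol states no figure to reproduce on this point. The check is a reading of the rules side by side, followed by a calculation for scale.

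**1. The bands**

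| Reading (mmol/l) | Infusion | Other steps |
|---|---|---|
| above 8 | not mentioned | bolus from Table 4 |
| above 6, up to 8 | not mentioned | none |
| 4–6 | stop | re-measure in 30 min |
| below 4 | not mentioned | 4 g glucose, recheck at 10 min, physician |
| below 2.3 | not mentioned | 50 g glucose, recheck at 10 min, physician |

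No sentence in the article says that the bands are cumulative or that the stop applies at or below 6.

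**2. Can a patient reach the low bands without first triggering the stop?**

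Yes, in two ways.

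- Routine readings are an hour apart, so glucose can fall from above 6 to below 4 between two of them. GIK patients above 8 mmol/l also receive Table 4 boluses (first bolus 2–10 IU, up to 22 IU after repeated rises).
- The first reading is taken 30 minutes before surgery, when the infusion is due to start. If it is below 4, no rule says to withhold the infusion.

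The article gives no data from which to estimate how often either happens.

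**3. Insulin delivered before the 10-minute recheck**

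From the protocol: I = (PG − 7)/(200/W) + 8 IU per 500 ml bag, run at 83 ml/h. Hence:

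- hourly insulin = I × 83/500
- insulin per 10 minutes = hourly insulin / 6

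Weight (W) and starting glucose (PG) below are assumptions.

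| PG (mmol/l) | W (kg) | I (IU) | IU/h | IU per 10 min |
|---|---|---|---|---|
| 6.1 | 120 | 7.46 | 1.24 | 0.21 |
| 6.1 | 60 | 7.73 | 1.28 | 0.21 |
| 8 | 80 | 8.4 | 1.39 | 0.23 |
| 10 | 80 | 9.2 | 1.53 | 0.25 |
| 12 | 120 | 11.0 | 1.83 | 0.30 |

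Worked example (PG 12, W 120): (12 − 7) × 120/200 + 8 = 11.0 IU; 11.0 × 83/500 = 1.83 IU/h; 1.83/6 = 0.30 IU.

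The same infusion carries glucose: 25 g × 83/500 = 4.15 g/h, or 4.15/6 = 0.69 g per 10 minutes, on top of the 4 g or 50 g rescue.

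**4. The low preoperative reading**

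The dose formula does not itself withhold insulin. At PG 3.5 and an assumed 80 kg it gives (3.5 − 7) × 80/200 + 8 = 6.6 IU, which is 6.6 × 83/500 = 1.10 IU/h, or 1.10/6 = 0.18 IU per 10 minutes.

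**The case against.** The best defence is that the rules form a ladder: stop at 4–6, add glucose and a physician below 4, add more glucose below 2.3. On that reading, an infusion that must stop at 5 must also stop at 3.5, and almost any clinician would stop it. The gap also largely closes itself. If the 10-minute recheck falls at 4–6, the stop applies as written; if it is still below 4, rescue and consultation apply again. Pump handling is, moreover, the kind of detail a journal article may leave to the full protocol.

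Much of this stands. It is why the harm is small and the grade is minor. It does not supply the missing instruction. The authors thought the stop needed writing at 4–6, and the need below 4 is greater. Nor is this a topic omitted for space: the article prints a rule for each low band and bounds the stop too narrowly. If the full protocol is clearer, the sponsor need only confirm it.

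Two stronger readings are not supported:

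- A reader might infer from "The assigned treatment will be continued up to 4 hours postoperatively", under Postoperatively, that the protocol orders insulin to run through hypoglycaemia. That sentence fixes when the assigned treatment ends, and the assigned GIK treatment includes its own stop and rescue rules. The text is silent at the low bands; it does not order the infusion to continue.
- A reader might infer that the hypoglycaemia comparison or the primary glucose outcome is distorted. Nothing in the document allows the frequency or size of such an effect to be estimated.

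**Conclusion.** The point holds as a minor safety-rule error. The GIK stop instruction is limited to 4–6 mmol/l, so readings the protocol defines as mild or severe hypoglycaemia, including one taken when the infusion is due to start, trigger rescue steps but no stated stop or do-not-start.

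Practical harm is probably small: a few tenths of a unit of insulin before the recheck, offset by the rescue glucose and by clinical judgement. That size rests on the assumed weights and starting glucose values and on the recheck happening on time. The conclusion about the wording rests on the article alone. Confidence is medium, because the full protocol is not shown. No effect on the primary outcome, sample size or power is claimed.

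**What to change.** Replace the GIK stop rule with one that has no lower limit and applies from the 30-minute preoperative reading onwards. Suggested wording:

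*If glucose is 6 mmol/l or lower, stop (or do not start) the infusion. At 4–6, re-measure in 30 minutes. Below 4 and below 2.3, also give the stated intravenous glucose, recheck at 10 minutes and call the research physician.*

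This keeps the 30-minute re-measurement, which is the only follow-up for the 4–6 band, and all existing rescue steps. The cost is one line of protocol text and a site instruction, with no extra patients, measurements or procedures.

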### Postoperatively

The assigned treatment will be continued up to 4 hours postoperatively. The patient will stay at the recovery room and will remain fasted. The treatment protocol will end 4 hours postoperatively. Hereafter, glucose will be monitored and treated according to the hospital protocol.

### Laboratory measurements

HbA1c, potassium and fasting serum glucose will be determined 1 h prior to surgery. Fasting serum glucose and potassium will be determined 1 hour, 4 hours and on day 1 postoperatively. When the patient has an arterial catheter during the surgical procedure, arterial glucose will be measured.

### Postoperative complications

The occurrence of postoperative complications will be assessed one month postoperatively. This will be determined via chart review and telephone contact. We will use a composite endpoint of postoperative complications derived from the RABBIT 2 surgery trial [19] and DelIT trial [22]. The definition of major and minor complications is shown in Tables 1 and 2. We used the definition of the centre for disease control (CDC) for the various infectious complications [23]. The occurrence of nausea and vomiting during hospital admission will be assessed and scored on the NRS scale. Diabetes related complications are shown in Table 3.

### Outcome measures

Our primary outcome measure is the difference in median serum glucose between the GIK, BR and LG arm 1 hour after surgery.

The secondary outcome measures are the difference in median serum glucose between the three study arms at 4 hours and 1 day postoperatively, the difference in the amount of insulin administered and difference in the occurrence of major, minor and diabetes related complications. the hourly measurements will be used to determine the perioperative area under the curve of the area outside the target range. In addition, the occurrence of mild or severe hypoglycaemia (glucose <4.0 mmol l^−1^ and <2.3 mmol l^−1^, respectively), hypokalaemia (<3.5 mmol l^−1^) or hyperkalaemia (>5.0 mmol l^−1^) is assessed. The difference in glucose variability, described as mean absolute glucose change (MAG), between study arms will be calculated [24]. The MAG is calculated by adding the absolute differences of the glucose values, divided by the time over which the measurements were taken.

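### MAG is not limited to the common hourly readings, so the 30-minute recheck that only the GIK arm receives pushes GIK glucose variability upward through sampling alone

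*Protocol article*

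**What the plan says.** All places are in the Protocol article.

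- **Common schedule** (Study procedures/interventions): "In all patients, capillary glucose will be measured every 60 minutes, starting 30 min prior to surgery".
- **GIK arm** (instructions below Table 4): "If glucose is 4–6 mmol l^−1^ stop infusion and measure again in 30 minutes". The BR and LG instructions give the 60-minute schedule and no 30-minute recheck.
- **Below 4 mmol/l** (Table 4 footnote): glucose is given and staff "measure again after 10 minutes and consult research physician". The footnote belongs to the shared algorithm, so this rule is common to all arms.
- **MAG** (Outcome measures): "The MAG is calculated by adding the absolute differences of the glucose values, divided by the time over which the measurements were taken". No restriction on the readings is stated.
- **AUC** (same paragraph): the hourly measurements are named as the input for the "perioperative area under the curve of the area outside the target range".
- **Hypoglycaemia** (same paragraph): mild is below 4.0 mmol/l and severe below 2.3 mmol/l, again with no limit on which readings count.

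**The concern.** MAG depends on how often glucose is sampled. If one arm is sampled more densely under a rule that the other arms lack, part of any MAG difference reflects the measurement schedule and not glucose control. The article fixes the input for the AUC and leaves it open for MAG, so a literal reading of the formula takes in the extra GIK values.

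The hypoglycaemia count has the same weakness. A GIK patient gets an additional look just when glucose is closest to the 4.0 limit, while a BR or LG patient with the same value waits a full hour. Low hypoglycaemia risk is the article's main argument for GLP-1 treatment (Background and Discussion), so unequal detection touches a comparison that readers will look for. Both effects work against GIK.

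**Working it through.** **Plan's own figure.** The article gives no figure for MAG. Its sample size supplies the number per arm used below. With SDs 1.8 and 2.4, a difference of 1 mmol/l, two-sided 5% (assumed two-sided) and 90% power:

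n = (1.8² + 2.4²) × (1.960 + 1.282)² / 1² = 9.00 × 10.51 ≈ 94.6, so 95 evaluable per arm. Then 95 × 1.1 = 104.5, rounded up to the stated 105 (dividing by 0.9 gives 106).

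**Direction.** Let a and c be consecutive hourly values and b the reading between them. Then |c − a| ≤ |b − a| + |c − b|. If the hourly schedule simply continues, elapsed time is unchanged. MAG therefore stays the same (b lies between a and c) or rises; it cannot fall.

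**Worked example.** Hourly values 7.5, 5.5, 6.5, 7.0, 7.5 over 4 h:

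- Hourly only: (2.0 + 1.0 + 0.5 + 0.5) / 4 = 1.00 mmol/l per h.
- With a 30-minute value of 5.0 after the 5.5: (2.0 + 0.5 + 1.5 + 0.5 + 0.5) / 4 = 1.25 mmol/l per h.

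**How often the recheck is triggered.** The article does not say. For a normal distribution, the share of readings in 4–6 is Φ((6 − mean)/SD) − Φ((4 − mean)/SD):

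| Mean, SD (mmol/l) | Source | Share in 4–6 |
|---|---|---|
| 8.7, 1.8 | Sample size calculation | Φ(−1.50) − Φ(−2.61) ≈ 6% |
| 9.7, 2.4 | Sample size calculation | Φ(−1.54) − Φ(−2.38) ≈ 5% |
| 7.0, 1.5 | Assumed | Φ(−0.67) − Φ(−2.00) ≈ 23% |
| 6.5, 1.5 | Assumed | Φ(−0.33) − Φ(−1.67) ≈ 32% |

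**Size of the bias.** Both arms were simulated from one autoregressive glucose process at 30-minute steps. Assumed inputs were 7 h of follow-up, hourly correlation 0.7–0.9 and meter SD 0.2–0.4 mmol/l. In GIK, a 30-minute reading was added after each hourly value of 4–6. The false-positive column is a two-sided rank test on MAG at 95 per arm, nominal 5%.

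| Glucose level | GIK MAG inflation | False positives | Extra patients with any value < 4.0 |
|---|---|---|---|
| Sample size section (8.7 ± 1.8; 9.7 ± 2.4) | about 2–4% | roughly 5–13% | 0.4–1.4 points |
| Means 6.5–7, SD 1.5 | 11–22% | about 67–98% | up to about 6 points (about 12% to 15% in one scenario at mean 7) |

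A second simulation with SD 1.8 over 6 h gave about 2% at a mean of 9, 5–7% at 8 and 11–13% at 7, so size and direction agree. The 10-minute rechecks below 4 mmol/l, common to all arms, were left out.

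**After the fix.** With MAG limited to the 60-minute readings, the inputs are the same in every arm and the artefact is zero by construction.

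**The case against.** The strongest reply is that this is a condensed article. It gives MAG one sentence and a citation, and the choice of readings for a derived secondary variable normally belongs in the analysis plan. Nothing says outright that unscheduled readings will enter. That is fair as to where the remedy belongs. It does not remove the point: the article states a formula, the formula depends on sampling frequency, and the same paragraph limits the inputs for one outcome but not the other.

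The second reply concerns size. The only glucose figures in the article come from an outside trial, and at those levels the inflation is a few per cent and the false-positive rate only modestly above nominal. This stands, and it makes calling MAG simply not comparable too strong. But those figures are not intraoperative values from this trial, and the bias grows as patients approach the 6–8 mmol/l that the article sets as its target.

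Third, lows found by the GIK recheck are real observations made under that strategy, so discarding them would lose safety information. This stands and shapes the fix.

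A reader might go further and infer two things that the document does not support:

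- **That the out-of-range AUC is also not comparable between arms.** It is restricted to hourly measurements and uses one range for all arms, so identical glucose gives the same expected AUC. A steady 5.0 and a steady 9.0 score alike because each is 1 mmol/l off target; that is the outcome's definition and applies equally in every arm.
- **That the 6–8 target contradicts the 4–8 row of Table 4.** The table's columns are insulin boluses, so the dash there means no bolus. Giving no insulin below the upper target limit is consistent with a 6–8 target, and the GIK instructions do act at 4–6.

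**Conclusion.** The point holds for MAG and, more weakly, for hypoglycaemia detection. The direction for MAG is certain if the rechecks enter the sum: GIK can only go up. The size rests on assumed glucose level, correlation, meter error and duration. It is small at the levels quoted for the sample size, but large enough to produce a false between-arm difference if patients run at 6.5–7 mmol/l. The true size cannot be derived from the article. The unequal detection of values below 4.0 is a difference in looking, not evidence that the GIK lows are spurious. Both outcomes are secondary; the primary outcome, serum glucose 1 hour after surgery, does not use these readings as planned.

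**What to change.** 1. State that MAG is computed from the scheduled 60-minute capillary readings common to all arms, leaving out the 30-minute GIK rechecks and the 10-minute rechecks after a low.
2. Keep hypoglycaemia detected at any time, in any arm, as the safety outcome.
3. Add a between-arm comparison of hypoglycaemia limited to the scheduled readings, so that readers can see how much of any GIK excess depends on the extra looks.

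Cost: a few sentences in the analysis plan, unscheduled readings leave the MAG, and one sensitivity analysis is added. Monitoring, treatment, sample size and the AUC definition need no change.

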### Statistical analyses

#### Sample size calculation

A 1 mmol l^−1^ decrease in glucose resulted in a relevant decrease in postoperative complications **(**8.7 mmol l^−1^ ± 1.8 and 9.7 ± 2.4) in the RABBIT 2 surgery trial [10]. We used the following formula to calculate the sample size: . Assuming a power of 90%, a significance level of 5% and a drop-out rate of 10%, we will need 105 patients per treatment group to detect a relevant difference of 1 mmol l^−1^ between treatment groups. Thus in total, we will need 315 patients.

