**Methods/Design:**

This is a multicentre randomised open label trial in patients with DM type 2 undergoing non-cardiac surgery. Patients are randomly assigned to one of three study arms; intraoperative glucose-insulin-potassium infusion (GIK), intraoperative sliding-scale insulin boluses (BR) or GPL-1 pre-treatment with liraglutide (LG). Capillary glucose will be measured every hour. If necessary, in all study arms glucose will be adjusted with an intravenous bolus of insulin. Researchers, care givers and patients will not be blinded for the assigned treatment. The main outcome measure is the difference in median glucose between the three study arms at 1 hour postoperatively. We will include 315 patients, which gives us a 90% power to detect a 1 mmol l^−1^ difference in glucose between the study arms.

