### Analyses

Statistical analyses will be performed using SPSS version 21.0 (SPSS Inc., Chicago, IL, USA). All data will be analysed according to an intention-to-treat analysis. No interim analysis is planned. Glucose is not normally distributed, thus the between group difference in median glucose at 1 hour, 4 hours and 1 day postoperatively will be tested with the Kruskal-Wallis test and post-hoc testing using the Mann–Whitney *U* test. In case of missing glucose at one hour, the last glucose measured during surgery will be carried forward. Change in glucose will be analysed using repeated measurements ANOVA, with time as fixed effect and baseline glucose, time and the interaction between treatments as covariates. Furthermore a per-protocol analysis will be performed next to the intention-to-treat analysis. Finally, the between group differences of the secondary outcomes will be tested with the ANOVA, Kruskal-Wallis, student *t*, Mann–Whitney *U* and the Chi-square test, where appropriate.

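### The stated 90% power is that of one two-arm comparison of means, not of the planned three-arm Kruskal-Wallis and Mann-Whitney procedure

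*Protocol article*

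**What the plan says.** The Sample size calculation section of the Protocol article takes two means and SDs from an earlier trial, 8.7 ± 1.8 and 9.7 ± 2.4 mmol/l (the SDs in "1.8 and 9.7 ± 2.4"). It then sets the design values: "Assuming a power of 90%, a significance level of 5% and a drop-out rate of 10" per cent. From these it concludes that "we will need 105 patients per treatment group to detect a relevant difference of" 1 mmol/l between treatment groups, and "Thus in total, we will need 315 patients". The formula itself is lost from the extracted text.

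The Abstract attaches the same figure to the whole trial: 315 patients, "which gives us a 90% power to detect a 1 mmol" per litre difference between the study arms.

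The Analyses section states that glucose is not normally distributed. It plans that the difference in medians across the three arms "will be tested with the Kruskal-Wallis test and post-hoc testing" by Mann-Whitney. It does not say outright that the pairwise tests depend on the overall result. A missing 1-hour glucose is replaced by the last intraoperative value.

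**The concern.** The power figure and the primary analysis are both fixed in this document, but they belong to different procedures. The sample size rests on two means, two SDs and one comparison. The analysis is a three-group rank test followed by pairwise rank tests. The calculation gives no mean for the third arm and makes no allowance for the rank test or for having to pass an overall test first.

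This matters because the Background section gives the aim as finding the optimal of three algorithms. A significant Kruskal-Wallis test alone does not say which arms differ, so the conclusion of interest needs the pairwise step. If the power for that step is below 90%, the chance of missing a true 1 mmol/l difference is larger than the 10% that the reader is told, and a null result would be given too much weight.

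**Working it through.** **Inputs.** From Sample size calculation: difference 1 mmol/l, SDs 1.8 and 2.4, power 90%, alpha 5%, drop-out 10%. From Randomisation: 1:1:1 allocation. From Analyses: Kruskal-Wallis, then Mann-Whitney.

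**Step 1: the protocol's own figure.** For two arms, two-sided 5%:

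n = (z₀.₉₇₅ + z₀.₉₀)² × (SD₁² + SD₂²)/δ² = (1.960 + 1.282)² × (3.24 + 5.76)/1² = 94.57, so 95 evaluable per arm (power 90.1%).

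Drop-out: 94.57/0.9 = 105.07, and 95 × 1.1 = 104.5, which rounds up to 105. The stated 105 is reproduced. A one-sided test gives 78 before drop-out and does not reproduce it.

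**Step 2: power of the planned analysis.** This was simulated with 20,000 replicates per scenario on normal data. The third arm's mean is an assumption, so two positions are shown: equal to one of the other arms, or midway. KW is Kruskal-Wallis at 5%. KW + pair also requires an unadjusted 5% Mann-Whitney test on the 1 mmol/l pair to be significant. The common SD is √(9/2) = 2.12.

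| Means; SDs | KW, n = 95 | KW + pair, n = 95 | KW, n = 105 | KW + pair, n = 105 |
|---|---|---|---|---|
| 8.7/9.7/9.7; 2.12 each | 91.5% | 85.8% | 94.2% | 89.5% |
| 8.7/9.7/9.7; 1.8/2.4/2.4 | 92.3% | 85.8% | 95.2% | 89.9% |
| 8.7/8.7/9.7; 1.8/1.8/2.4 | 89.8% | 85.7% | 92.6% | 89.0% |
| 8.7/9.2/9.7; 2.12 each | 81.2% | 80.4% | 85.4% | 84.8% |
| 8.7/9.2/9.7; 1.8/2.1/2.4 | 81.9% | 81.0% | 86.0% | 85.2% |

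A single Mann-Whitney test on the pair, without the overall test, has 88% at n = 95 and 91–92% at n = 105.

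**Step 3: analytic check.** The three-group F test has noncentrality n × Σ(μᵢ − μ̄)²/σ², with σ² = 4.5. At n = 95:
- one arm apart: 95 × 0.667/4.5 = 14.1, power 92.7%;
- third arm midway: 95 × 0.5/4.5 = 10.6, power 83.3%.

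The Kruskal-Wallis figures for the common SD lie one to two points lower, as expected for a rank test on normal data.

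**Step 4: skewed data.** Log-normal data matched to the same means, with the arm-specific SDs, give 75–82% for KW + pair at n = 95. With the common SD they give 85–90%. The low figures come partly from the matching. The median of a log-normal variable is mean/√(1 + (SD/mean)²), so the medians are 8.52 and 9.42, a difference of only about 0.90 mmol/l.

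**The case against.** Sizing one pairwise comparison in a three-arm trial is common practice, and a difference between treatment groups reads naturally as pairwise. On that reading the shortfall is small, since an unadjusted Mann-Whitney test on one pair has 88%. The Analyses section names Kruskal-Wallis as the main test. If one arm stands apart from two equal arms, that test keeps about 90–92%, so the advertised figure is met. All randomised patients are analysed and a missing 1-hour value is carried forward, so the number analysed may be nearer 105 than 95. KW + pair then reaches 85–90%. An article may also condense a fuller justification.

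Much of this stands, and it limits the point. It does not remove it: the 90% is tied neither to a third-arm pattern nor to a definition of detection, and under normal data KW + pair does not exceed 90% in any pattern examined, even with 105 per arm.

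Stronger readings are tempting, but the document does not support them:
- A reader might infer that power is about 75%. That needs an assumed log-normal shape, matched so that the median difference falls below the stated 1 mmol/l, together with a midway third arm.
- A reader might infer that optimal means beating both other arms, which would lower power further. No decision rule in the document requires two significant pairs.
- A reader might apply a Bonferroni split over three pairs. None is stated, and with three arms a 5% overall test followed by 5% pairwise tests already controls the family-wise error.
- A reader might call the drop-out step wrong. Since 94.57/0.9 = 105.07 and the formula is not visible, at most one patient per arm is in question.

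**Conclusion.** The mismatch is real and of moderate weight. The 90% belongs to a two-arm normal comparison with 95 evaluable per arm. For identifying a pair of arms that differ by 1 mmol/l, the planned procedure has about 80–81% power if the third arm is midway and about 86% if it equals one of the other two. The chance of missing the difference is therefore 14–20%, not 10%. If carry-forward keeps 105 per arm, power is 85–90%.

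These figures assume normal data, the protocol's SDs, an assumed third-arm position, and pairwise tests that count only after a significant overall test. With skewed glucose they may be lower, depending on the shape and the SDs. It would go too far to say that the design cannot reach 90% on any reading, because the overall test alone does so when one arm is clearly lower than two equal arms. The fault is that the figure is stated without that condition.

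**What to change.** Keep 315 patients. In the sample size section:
- state where the third arm is assumed to lie;
- replace the unqualified 90% with the power of the Kruskal-Wallis and Mann-Whitney procedure: about 80–86% for identifying a 1 mmol/l pair with 95 evaluable per arm, depending on the third arm;
- if a figure for the overall test alone is also wanted, give it with its pattern (about 90–92% for one arm apart, about 81–82% for a midway third arm).

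Make the power statement in the Abstract agree. In the Analyses section, state that pairwise Mann-Whitney tests at 5% are run only after a significant Kruskal-Wallis test, and that with three arms this needs no further split of alpha.

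The cost is a few sentences and a slightly less favourable stated power. No extra patients or data are needed.
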